### Statistical Analysis

#### Statistical and Analytical Plans

Baseline participant characteristics will be reported and described using summary statistics—mean and standard deviation for continuous data and number and proportion for categorical data. The primary analysis to determine if there is a statistically significant effect of intranasal ketamine on depressive symptoms will be the paired 1-tailed *t* test of the HDRS-24 score at baseline to week 4. We will also report the standardized mean difference as a measure of effect size (small: 0.2; medium: 0.5; large: 0.8 [40]). For tolerability and safety outcomes, we will report the number and proportion of individuals who experience a transient increase in blood pressure, agitation, and behavioral disturbance. To assess suicidality change, we will use the 1-tailed paired *t* test from baseline to week 4 of the Scale of Suicide Ideation score and calculate the standardized mean difference. For neurophysiology, we will use the 1-tailed independent *t* test to compare components of TMS-evoked responses at left dorsolateral prefrontal cortex. In addition, we will use the nonparametric cluster-based permutation test to investigate any significant changes in overall EEG channels.

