**Objective:**

The objective of this open-label pilot clinical trial is to test the feasibility and safety of intranasal ketamine in patients who have not responded to electroconvulsive therapy. The primary outcome is to determine the feasibility of a larger randomized controlled trial to test the efficacy of intranasal ketamine for patients who have not responded to electroconvulsive therapy for clinical indicators in unipolar depression. The secondary outcome is to determine the preliminary effects of an intervention on clinical outcomes, such as depressive symptoms, suicidal ideation, and quality of living. The third outcome is to explore neurophysiological changes as measured by transcranial magnetic stimulation electromyography and electroencephalography to measure changes in cortical excitability as potential predictors of clinical response.

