## Methods

### Design

This is an open-label pilot study to assess the feasibility of conducting a randomized controlled trial to test the safety, tolerability, and efficacy of intranasal ketamine in patients with treatment-resistant depression who did not respond or were not able to tolerate a course of acute electroconvulsive therapy.

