### Study Measurements

Given that this trial recruits participants who received at least one electroconvulsive therapy session, and therefore, underwent blood work, electrocardiography, and medical clearance by anesthesia services in accordance with standard clinical procedures, we will use these parameters for this trial. The results will be available for screening and review by the study’s medical doctor prior to the start of treatment. Tests completed within the 6 months prior to screening will be used unless new medical symptoms requiring further investigation emerge, in which case, the tests will be repeated. Blood tests will include complete blood count with differential tests (white blood cells, red blood cells, hemoglobin, hematocrit, mean corpuscular volume, mean corpuscular hemoglobin, mean corpuscular hemoglobin concentration, red cell distribution width, mean platelet volume, platelet, nucleated red blood cell count, neutrophil count, lymphocyte count, monocyte count, eosinophil count, basophil count) and blood chemistry tests for liver function (alanine aminotransferase, aspartate aminotransferase), kidney function (blood urea nitrogen, creatinine), electrolyte levels (sodium, potassium, chloride, phosphate), and thyroid function (thyroid-stimulating hormone). Electrocardiography results will be reviewed by the study’s medical doctor. Participant blood pressure will also be monitored before, during, and after treatment.

Clinical assessments will include (1) the Mini-International Neuropsychiatric Interview, to assess current and lifetime depression and other psychiatric disorders and to clarify psychiatric inclusion and exclusion criteria; (2) the 24-item Hamilton Rating Scale for Depression [28], as the primary outcome measure (and a score greater than or equal to 14 will be used to establish eligibility at study entry); (3) the Scale of Suicide Ideation [29], administered at baseline, weekly, at posttreatment, and at follow-up to monitor for any safety concerns and a secondary outcome measure to assess suicidality; and the(4) World Health Organization Disability Assessment Schedule 2.0 [30], used as a standard measure of disability promoted and administered at baseline and posttreatment to assess changes in individual level of functioning.

Demographic information, medical history, concomitant medications, and antidepressant treatment history form information will also be assessed.

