## Discussion

To our knowledge, this is the first study to test repeated doses of rketamine delivered intranasally in patients with major depressive disorder who did not respond (either clinically or due to their inability to tolerate) to an acute course of electroconvulsive therapy. The use of neurophysiological tools to assess changes in cortical excitability will provide preliminary data for potential biomarkers of response, which can be further assessed in a larger clinical trial. A lack of control group and small sample size are limitations of the current protocol. However, given that it is a pilot open-label clinical trial, the sample size is sufficient (ie, the goal is not to assess generalizability or statistical significance). The lack of blinding in the control group is a common concern in ketamine trials [27], because a placebo with comparable effects does not exist, and it is impossible to ensure blinding to the full extent. Because the study is being conducted at a single site of a large psychiatric academic facility, the results may not be transferable to a broader population.

Results will be presented during scientific conferences, in clinical rounds, and publications in relevant journals.

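### The protocol names feasibility as its primary outcome, but its only primary analysis is an uncontrolled significance test on the depression scale

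*Protocol article*

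**What the plan says.** Four parts of the protocol article bear on which outcome is primary.

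- **Abstract, Objective.** "The primary outcome is to determine the feasibility of a larger randomized controlled trial". Clinical effect is placed below it: "The secondary outcome is to determine the preliminary effects of an intervention on clinical outcomes, such as depressive symptoms".
- **Methods, Design.** The purpose matches the Abstract: "This is an open-label pilot study to assess the feasibility of conducting a randomized controlled trial". Safety, tolerability and efficacy are described as what that later trial would test.
- **Study Measurements.** The list of clinical assessments gives a different primary outcome: "the 24-item Hamilton Rating Scale for Depression [28], as the primary outcome measure".
- **Statistical and Analytical Plans.** One analysis is called primary: "The primary analysis to determine if there is a statistically significant effect of intranasal ketamine on depressive symptoms". The method "will be the paired 1-tailed *t* test of the HDRS-24 score at baseline to week 4". A standardized mean difference accompanies it. The section then covers counts and proportions for safety and tolerability, a test on the suicide ideation scale, and the neurophysiology.

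The Discussion adds that a small sample is sufficient for a pilot because "the goal is not to assess generalizability or statistical significance". The article uses both HRSD-24 and HDRS-24 for the Hamilton scale; I read them as the same instrument.

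**The concern.** A trial's primary analysis should answer the question its primary outcome poses. Here the outcome named primary is feasibility, while the analysis named primary is a test of efficacy on an outcome the Abstract ranks second. The reason given for accepting 25 participants also disowns the kind of inference that this analysis is set up to make.

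There is a second difficulty in the wording. The test is meant to show an effect of the drug, yet the study has one arm. A fall in Hamilton score between baseline and week 4 mixes any drug effect with regression to the mean (entry requires a raised score), expectancy under open-label treatment, and the natural course of the episode. A small p value would show that scores changed, not that ketamine changed them.

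At stake is how the pilot is read. Followed as written, its headline result would be a p value for an uncontrolled change, presented as a drug effect.

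**Working it through.** **1. The plan's own figure.** The Sample Size section gives about 250 new patients a year, 25% to 30% nonresponse or intolerance, 20% of those eligible, and 24 months.

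- Lower bound: 250 × 0.25 × 0.20 × 2 = 25
- Upper bound: 250 × 0.30 × 0.20 × 2 = 30

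The stated 25 reproduces at the lower bound. It is a recruitment projection. No alpha, power, effect size, SD or target precision enters it, so the number is tied neither to the t test nor to the precision of any feasibility measure.

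**2. The statements side by side.**

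| Question | One answer | The other answer |
|---|---|---|
| What is primary? | Feasibility (Abstract, Objective; consistent with Design) | Hamilton scale (Study Measurements; primary analysis) |
| Rank of depressive symptoms? | Secondary (Abstract, Objective) | Primary (Study Measurements; primary analysis) |
| Is statistical significance a goal? | No (Discussion, defending the sample size) | Yes (stated purpose of the primary analysis) |

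Each row needs one side to give way.

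**3. What the primary test would detect without a drug effect.** The article gives n = 25 and a one-tailed test. It gives no alpha and no figure for non-drug change. I assume a one-tailed 5% level, 25 complete pairs, a drug effect of zero, and non-drug improvement of d SDs of the change score, for d = 0.2, 0.5 and 0.8. These are the small, medium and large benchmarks that the analysis section itself lists for effect size; they are not estimates for this population.

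- Critical value: t(0.95; 24 df) = 1.711
- Smallest mean change declared significant: 1.711 / √25 = 0.342 SD of change
- Noncentrality: d × √25
- Probability of significance: 1 − F(1.711), where F is the noncentral t distribution function with 24 df

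| Assumed non-drug change (SD) | Noncentrality | Probability, one-tailed 5% | Same, upper tail of a two-sided 5% test |
|---|---|---|---|
| 0.2 | 1.0 | 25% | 16% |
| 0.5 | 2.5 | 78% | 67% |
| 0.8 | 4.0 | 99% | 97% |

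The one-tailed choice raises the figures, but a two-sided test does not cure the problem.

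**4. What 25 participants give for a feasibility proportion.** Exact (Clopper-Pearson) 95% intervals for hypothetical counts are 18/25 = 72% (51% to 88%), 20/25 = 80% (59% to 93%) and 22/25 = 88% (69% to 97%). The middle interval is about 34 percentage points wide, so these estimates are coarse, but they concern the outcome the Abstract names as primary.

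**The case against.** Several points on the other side are sound and limit what can be said.

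- **The full protocol or SAP may define feasibility metrics and progression rules.** This is a condensed article, and those documents are not shown. A reader might infer that feasibility will never be analysed. The article does not support that, because the absence of metrics from it is not evidence that none exist. What survives is that the article does not leave the primary analysis open. It fixes one, on the outcome ranked second, and an SAP could not follow every section at once.
- **Part of the objective is analysed.** The Abstract's objective includes safety, and the analysis section gives descriptive counts for safety and tolerability. It would be wrong to say that the trial's whole question goes unanalysed.
- **Nothing ties the decision to run the larger trial to the p value.** A reader might expect that decision to rest on it. The Abstract's Conclusions say only that results will inform the larger trial's development.
- **The trial was not sized for feasibility either.** The 25 is a recruitment projection, so it cannot be argued that the t test displaces an outcome for which the sample was chosen.
- **The lack of a control group is acknowledged.** The Discussion lists it as a limitation, and the Abstract calls the clinical effects preliminary. That softens the causal point but leaves the wording of the primary analysis untouched.
- **Primary might mean the primary clinical measure.** This is plausible, but neither Study Measurements nor the analysis section adds that qualifier.
- **The size rests on assumptions.** This is true. The article offers no figure for non-drug change in patients whom electroconvulsive therapy did not help, and at the low end the probability is only about one in four.

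The Feasibility section under Methods does not settle the matter. It argues in advance that recruiting 25 people is achievable and specifies no outcome or analysis.

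**Conclusion.** The concern holds as an internal contradiction on the primary outcome, and it should be corrected. The Abstract and Design make the trial a feasibility study; Study Measurements and the analysis section make the Hamilton scale primary; and the Discussion disclaims the significance goal that the primary analysis states. This rests on the text alone and needs no assumption.

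The added point, that an uncontrolled pre-post test cannot be read as an effect of ketamine, follows from the single-arm design. Its size is illustrative: about 25%, 78% or 99% probability of a significant result with no drug effect, for assumed non-drug change of 0.2, 0.5 or 0.8 SD, at an assumed one-tailed 5% level with all 25 participants contributing. The range is wide because the article gives nothing to narrow it.

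**What to change.** 1. State feasibility of the larger trial as the primary outcome throughout, and label a descriptive feasibility summary as the primary analysis. Suitable contents are recruitment against 25 in 24 months, the proportion completing the 8 sessions, and the proportion with a week-4 assessment, with exact 95% confidence intervals for the proportions. If the full protocol or SAP already defines feasibility metrics, use those.
2. In Study Measurements and in Statistical and Analytical Plans, relabel the Hamilton scale as a secondary clinical outcome. Report mean change from baseline to week 4 with a two-sided 95% confidence interval, alongside the standardized mean difference already planned.
3. In the analysis section, describe the quantity as change from baseline, not as an effect of intranasal ketamine.
4. The Discussion's sentence on statistical significance can then stand, since it will agree with the analysis.

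The cost is a few wording changes and a short table. Recruitment, session attendance and week-4 completion are recorded in the ordinary running of the trial, and treatment, visits and sample size are unaffected. The one thing given up is the primary status of the Hamilton p value.

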In this study, we aim to assess the safety and feasibility of intranasal rketamine in patients with unipolar depression who did not respond to the acute course of electroconvulsive therapy to inform a larger randomized controlled trial and examine potential neurophysiological biomarkers of response. TMS- electromyography (EMG) and electroencephalography (EEG) paradigms can be used to investigate the impact of ketamine on cortical activities via intracortical facilitation and short-interval cortical inhibition paradigms [19,22-26]. Based on accumulating evidence supporting the efficacy and tolerability of ketamine, we hypothesize that intranasal rketamine administered twice per week over 4 weeks will (1) result in improvement in depressive; (2) be safe and well tolerated in patients with treatment-resistant depression who could not tolerate or have not responded to electroconvulsive therapy; (3) result in neurophysiological changes. The results of this study will provide an important characterization of the neurophysiological effects of rketamine on cortical neurophysiology [19,22-26], which may serve as a ketamine biomarker and would be a crucial breakthrough in determining potential predictors of clinical response for depression.

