### Ethics Approval

This study has received Centre for Addiction and Mental Health (CAMH) research ethics board (095-2019) and Health Canada approval. For this pilot trial, all relevant adverse events and all serious adverse events will be reported if they meet applicable reporting requirements. All data monitoring, auditing, and harms reporting will be performed according to CAMH research ethics board and regulatory standards.

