#### Potential Risks and Mitigation Strategies

Given the potential risks described below, trained medical personnel will be present during the administration and for the entire duration of the 2-hour monitoring period.

Drug-related risks include (1) psychiatric symptoms such as fatigue, dizziness, anxiety, visual and auditory disturbances, panic attacks, increased irritability, or changes in mood and behavior; (2) medical symptoms such as transient increases in blood pressure and heart rate, an increase in need to urinate, headaches, vision changes, chest pain, shortness of breath, confusion, memory impairment, anaphylaxis; and (3) rare risk of dependency. Ketamine is classified as a schedule I controlled substance due to its potential for abuse and addiction and can be abused in a number of ways, including via injection, snorting, or orally [8]. Ketamine can produce vivid dreams and feel that the mind is separated from the body. Regular users of ketamine can become tolerant to the dissociative effects of the drug, meaning more and more is needed to achieve the same effect [8]. To address these risks, in this trial, ketamine will be dispensed by the research pharmacy and administered by a trained medical professional, and the patient will receive close supervision and monitoring. Doses are individually calculated, and treatment sessions are structured to prevent tolerance building. Patients will be strongly discouraged from using ketamine outside of the context of this trial and will be informed that if they have more questions, they can be discussed with their medical provider or study physician.

A potential risk in clinical assessments is that answering multiple questions can, at times, be distressing. These adverse reactions are primarily brief and transient and rarely have any long-term implications.

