Monitoring assessment during treatment sessions will include (1) vital signs collected every 30 minutes during a 2-hour monitoring session (blood pressure, heart rate, and oxygen levels) and (2) behavior changes assessed through observation.

Neurophysiological assessments will include (1) the Transcranial Magnetic Stimulation Adult Safety Screen to assess for potential TMS risk factors; and (2) TMS-EMG/EEG (Multimedia Appendix 2). Our neurophysiological measures have been established and have a high test–retest reliability (ie, intraclass correlation >0.9) [31,32]. Data analysis will be performed using semiautomated methods developed and validated by our group [31,32]. TMS pulses will be administered to the left dorsolateral prefrontal cortex, using a figure-of-eight coil (7 cm), and 2 Magstim 200 stimulators (Magstim Company Ltd) connected via a Bistim module, and motor evoked potential data will be collected using commercially available software (Signal, Cambridge Electronics). Each TMS session will include the establishment of the individual threshold for stimulation motor cortex, and dorsolateral prefrontal cortex localization will be performed according to previously published methods [31,32]. Resting motor threshold will be determined by applying single pulses of TMS to the motor cortex while the coil is placed at the optimal position to elicit motor evoked potentials from the right abductor pollicis brevis muscle. The resting motor threshold is defined as the minimum stimulus intensity that elicits a motor evoked potential of >50 μV in more than 5 of the 10 trials [33,34]. Electromyography will be recorded from the abductor pollicis brevis with Ag–AgCl electrodes placed over the belly of the muscle. The signal will be amplified (Intronix Technologies Corporation Model 2024F), filtered (bandpass 2 Hz-5 kHz), digitized at 5 kHz (Micro 1401, Cambridge Electronics Design), and stored in a laboratory computer for offline analysis. The participants will be instructed to relax throughout the study. Trials contaminated with voluntary muscle activity will be discarded.

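### The named safety summary covers three event types and is narrower than the article's own drug risks, collected vital signs and safety discontinuation criteria

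*Protocol article*

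**What the plan says.** The Objective in the abstract is to "test the feasibility and safety of intranasal ketamine in patients who have not responded to electroconvulsive therapy". The Introduction's second hypothesis is that the treatment will "be safe and well tolerated in patients with treatment-resistant depression who could not tolerate or have not responded to electroconvulsive therapy".

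Statistical and Analytical Plans gives one sentence to tolerability and safety: "we will report the number and proportion of individuals who experience a transient increase in blood pressure, agitation, and behavioral disturbance". The same section tests the change in the Scale of Suicide Ideation separately. Study Measurements says that scale also serves safety monitoring.

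Potential Risks and Mitigation Strategies describes a much wider set of harms:
- psychiatric: "psychiatric symptoms such as fatigue, dizziness, anxiety, visual and auditory disturbances, panic attacks, increased irritability, or changes in mood and behavior";
- medical: "transient increases in blood pressure and heart rate, an increase in need to urinate, headaches, vision changes, chest pain, shortness of breath, confusion, memory impairment", and anaphylaxis;
- dependency, as a rare risk;
- dissociation: "Ketamine can produce vivid dreams and feel that the mind is separated from the body".

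Study Measurements has blood pressure, heart rate and oxygen levels recorded every 30 minutes over the 2-hour monitoring period, with "behavior changes assessed through observation". Discontinuation Criteria lists several safety reasons for stopping, among them marked worsening of depression, hospital admission for suicidality, seizure and unstable medical illness.

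Ethics Approval adds that "all relevant adverse events and all serious adverse events will be reported if they meet applicable reporting requirements", and that harms reporting follows ethics board and regulatory standards.

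**The concern.** The article does not leave the safety outcomes to another document. It names them, and the names do not match what it says elsewhere about the drug's risks, what is measured at each session, and why a participant may be stopped. An analyst who follows the sentence literally would tabulate three event types. The trial could then report on its safety hypothesis with no table of dissociation, cognitive effects, serious adverse events or withdrawals for adverse events.

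This matters because the pilot is meant to inform a randomized trial of safety, tolerability and efficacy, whose planners need those figures. It also matters for this population. The eligibility criteria describe intolerance of electroconvulsive therapy partly through confusion, cognitive impairment and worsening anxiety. Confusion, memory impairment and anxiety reappear among the drug's risks, yet none is named in the safety summary.

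**Working it through.** No stated figure is in dispute, so the check is mainly a comparison of the article's sections.

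**1. Described risks against the named list.** I counted visual and auditory disturbances as one item, mood and behavior changes as one, and blood pressure and heart rate as two.

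| Group | Items described | Named directly in the summary | Possible overlap |
|---|---|---|---|
| Psychiatric | 7 | 0 | 2 (irritability with agitation; mood or behavior change with behavioral disturbance) |
| Medical | 10 | 1 (blood pressure) | 0 |
| Dependency | 1 | 0 | 0 |
| Vivid dreams, dissociation | 2 | 0 | not determinable |

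The total is 7 + 10 + 1 + 2 = 20 items. One is named and two may overlap, which leaves 20 − 1 − 2 = 17 with no clear counterpart. The count depends on how items are split, and agitation and behavioral disturbance are broad, undefined terms. It shows the direction and rough extent of the gap, not an exact ratio.

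**2. Session data against the named list.** Readings every 30 minutes for 2 hours give 120 / 30 = 4 post-dose readings per session, not counting one at time zero. Over 8 sessions that is 4 × 8 = 32 readings per participant who completes treatment. Blood pressure has a planned summary, for transient rises. Heart rate and oxygen levels have none. No instrument for dissociation is named, and observing behavior may miss a subjective experience.

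**3. Discontinuations against the named list.** The criteria include several safety reasons for stopping. The analysis section names no count of participants stopped for them.

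**4. The wider provision.** The Ethics Approval text depends on reporting requirements being met and concerns ethics and regulatory reporting. It does not say that the trial's results will tabulate adverse events.

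**5. Would 25 participants show such events?** The chance of at least one affected participant is 1 − (1 − p)^25. The true risks p below are assumptions; the documents give none.
- p = 5%: 1 − 0.95^25 = 0.72.
- p = 10%: 1 − 0.90^25 = 0.93.

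Harms at these rates would probably occur in this trial, so whether they are tabulated is a practical question.

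**6. Why intervals help.** For 0 of 25, the exact two-sided 95% upper limit is 1 − 0.025^(1/25) = 13.7%. For 1 of 25, the exact interval is 0.1% to 20.4%. These limits reflect the sample size. They do not measure the effect of the narrow list.

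**The case against.** The strongest reply is that this argues from silence in a condensed article. The analysis sentence says what will be reported and does not say that nothing else will be. Adverse-event tables, the safety population and participant flow are commonly left to the full protocol or analysis plan, neither of which is shown. Ethics Approval does provide for harms reporting. The risk section explains risks and their mitigation, so a shorter analysis list does not contradict it. Suicidality is analysed separately, and behavioral disturbance may capture some overt dissociation or panic.

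Much of this stands, and it limits the point. A reader might infer that the trial will declare the drug safe without looking at the other harms. The documents do not support that: they contain no exclusive wording and no decision rule for safety. A reader might also infer that a zero count would be presented as proof of safety. That is speculation, since the Discussion acknowledges the small sample and the absence of a control group.

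A reader might further want to count missed dose-escalation steps as tolerability failures. The article adjusts dose on clinical response as well as tolerability, so such a count would mix the two.

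What does not stand is the claim that the matter is simply left elsewhere. The article specifies its safety outcomes, and more narrowly than its own account of harms. A fuller plan, if there is one, would have to be reconciled with that sentence.

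**Conclusion.** The point holds in a limited form. The named safety summary is narrower than the article's own risks, collected vital signs and safety discontinuation criteria, and the only wider provision is conditional reporting to oversight bodies. A conclusion of safe and well tolerated that rests on the analysis section as written could omit important harms. The documents do not show that it would.

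The size is one of scope: about 17 of 20 described items have no clear counterpart in the summary, two of the three monitored vital signs are not summarised, and safety discontinuations are not counted. This assumes that the analysis sentence is followed literally and that the undefined terms do not absorb most of the listed symptoms. It is a worthwhile and inexpensive correction, and it does not invalidate the design.

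**What to change.** In Statistical and Analytical Plans, define the safety summary among all participants who receive at least one dose. Report the number and proportion, each with an exact 95% confidence interval, with:
- any adverse event;
- any serious adverse event;
- dissociation, and each other risk described in Potential Risks and Mitigation Strategies, as recorded;
- discontinuation due to an adverse event.

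Add a descriptive summary of the heart rate and oxygen data. Keep the three events already named as events of special interest. Intervals for every risk at every session are not needed in a sample of 25.

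The cost is a larger descriptive table, drawn mostly from monitoring and records the trial already has. Dissociation may need to be asked about explicitly during the existing 2-hour monitoring, because no instrument for it is named. No dose or clinical rule is affected. If a fuller analysis plan already contains these tables, it is enough to align the article's sentence with it.

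### One-tailed t tests do not fit the non-directional neurophysiology hypothesis or the safety role of the suicide-ideation scale, and the article gives no direction for either

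*Protocol article*

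**What the plan says.** The Protocol article, under Statistical and Analytical Plans, names three t tests, all one-tailed.

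- Depression: the primary analysis "will be the paired 1-tailed *t* test of the HDRS-24 score at baseline to week 4".
- Suicidality: "To assess suicidality change, we will use the 1-tailed paired *t* test from baseline to week 4 of the Scale of Suicide Ideation score", after which the authors will "and calculate the standardized mean difference".
- Neurophysiology: "we will use the 1-tailed independent *t* test to compare components of TMS-evoked responses at left dorsolateral prefrontal cortex". Beside it stands a "nonparametric cluster-based permutation test to investigate any significant changes in overall EEG channels", for which no sidedness is given.

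The section states no significance level, no reason for one-tailed testing, and no direction for any TMS-evoked component.

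The end of the Introduction sets out the hypotheses. The one on depression is directional: "1) result in improvement in depressive". The one on neurophysiology is not: "3) result in neurophysiological changes". Suicidality appears in none of them. The Abstract (Objective) lists suicidal ideation among the clinical outcomes on which preliminary effects are sought, and describes the neurophysiological aim as exploratory.

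Study Measurements gives the Scale of Suicide Ideation two purposes: "to monitor for any safety concerns and a secondary outcome measure to assess suicidality". It is collected at baseline, weekly, after treatment and at follow-up.

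**The concern.** A one-tailed test needs a direction fixed beforehand, and results in the other direction must be of no interest. Neither condition is visibly met for two of the three measures.

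For neurophysiology, the hypothesis and the companion permutation test both look for change in either direction. With no tail named, the article does not prevent its being chosen once the estimates are known.

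For suicidality, the direction that a safety measure must be able to show is a rise. A one-tailed test for improvement returns the same non-significant result whether the mean is unchanged or clearly worse. The safety sentence in the analysis section does not fill the gap: its listed outcomes are blood pressure, agitation and behavioral disturbance, not suicidality. Potential Risks and Mitigation Strategies names mood and behavior changes among the drug risks, so worsening is foreseeable.

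**Working it through.** **The plan's own figure.** The Sample Size section derives 25 participants from recruitment capacity: 250 patients per year × 2 years × 0.25 × 0.20 = 25.0 (30.0 with the 30% rate). This reproduces the stated number. It uses no significance level, power or effect size, so the choice of sidedness does not affect it.

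**Question set against test.**

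| Measure | Stated question | Stated test | Match |
|---|---|---|---|
| HDRS-24 | Improvement | One-tailed paired | Yes |
| Scale of Suicide Ideation | Change; also safety monitoring | One-tailed paired | No, for the safety role |
| TMS-evoked components | Change, no direction | One-tailed independent | No |

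**Inputs for the arithmetic.** n = 25 complete pairs, df = 24 (recruitment target, no dropout: an assumption). Level 5% (assumed). Effects of 0.5 and 0.8, the article's medium and large benchmarks, taken here in SDs of within-person change. The suicide-scale test is taken to look for improvement.

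**Type I error.**
- Direction fixed in advance: P(T > t₀.₉₅) = 0.05. A simulation of 400,000 samples of 25 gave 0.0503.
- Tail chosen after seeing the data: P(|T| > t₀.₉₅) = 2 × 0.05 = 0.10. The same simulation gave 0.0997.

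The doubling follows from the symmetry of the null t distribution and does not depend on df. It therefore carries over to the independent t test for each component, provided that its statistic follows its reference distribution.

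**Threshold, paired tests only.** Smallest observed change called significant = critical t / √25.
- One-tailed 5%: 1.711 / 5 = 0.342 SD.
- Two-sided 5%: 2.064 / 5 = 0.413 SD.

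**Power, paired tests only** (noncentral t, noncentrality = effect × √25):

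| True effect (SD of change) | One-tailed 5%, improvement | Two-sided 5%, same improvement | Two-sided 5%, same-sized worsening | One-tailed test, declares worsening |
|---|---|---|---|---|
| 0.5 | 78% | 67% | 67% | never |
| 0.8 | 99% | 97% | 97% | never |

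**Other possible level.** At one-tailed 2.5% the improvement threshold is t = 2.064, the same as two-sided 5%. The leniency disappears, but the test still cannot declare worsening.

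The thresholds and powers apply to the HDRS-24 and suicide-scale tests. They do not describe the independent neurophysiology comparison.

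**The case against.** A reader might infer that error rates are understated throughout. The documents do not support that. A one-tailed test with a preset direction holds its nominal level, and no level is stated against which an understatement could be measured. The depression hypothesis predicts improvement, so its one-tailed test is consistent with it. Preferring two-sided testing there is convention.

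A reader might also infer that worsening would go unseen. That is true only of the p-value. The standardized mean difference has a sign, the suicide scale is scored weekly, and Discontinuation Criteria covers a sustained rise in HDRS-24, hospitalization for suicidality and clinically significant worsening of mood. The t test can also be read as serving the scale's effect role, with weekly monitoring serving safety. A mean test in 25 uncontrolled participants is in any case a weak harm detector, because one or two deteriorations can be hidden by average improvement.

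On neurophysiology, a fuller protocol or analysis plan may fix a direction for each component, and the Introduction cites findings of impaired inhibition and excitation that could motivate one. The outcome is exploratory, and the Discussion says that significance is not the trial's goal.

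Most of this stands and limits the point. It does not remove it. The article chose one-tailed tests where its own stated questions are two-directional. Discontinuation rules protect individuals but are not an analysis, and people removed under them may have no week-4 score for the paired test. Nor does the disclaimer about significance justify the more lenient threshold, since the analysis section makes a significance test on HDRS-24 its primary analysis.

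**Conclusion.** The point holds for two measures. The one-tailed test of TMS-evoked components does not match a non-directional hypothesis, and the one-tailed test of the Scale of Suicide Ideation does not serve the safety role that the article gives it, because it cannot declare a mean rise.

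The size is conditional. The 10% error per component arises only if the tail is picked after seeing the data, at an assumed 5% level. The documents do not show that this will happen, only that the article does not rule it out. For the suicide scale, what is lost is the ability to flag a mean worsening, which a two-sided 5% test would detect with 67% probability at 0.5 SD and 97% at 0.8 SD, given 25 complete pairs.

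The HDRS-24 test is lenient (0.34 rather than 0.41 SD of change if the level is one-tailed 5%) but valid. The sample size and the feasibility aim are unaffected. This is a modest point, worth correcting because the correction is easy.

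**What to change.** Under Statistical and Analytical Plans:

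1. State the significance level.
2. Make the TMS-evoked component comparisons and the Scale of Suicide Ideation test two-sided, each with a two-sided 95% confidence interval.
3. Preferably give a two-sided 95% interval for the HDRS-24 change as well, for consistency.
4. Add to the safety reporting the number and proportion of participants whose suicide-ideation score rises from baseline at any weekly visit. This shows individual deterioration that a mean can hide.

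The cost is wording and one extra tabulation from scores already collected. If one-tailed 5% was intended, power for a two-sided paired test with n = 25 falls by 11 percentage points at 0.5 SD (78% to 67%) and 2 points at 0.8 SD (99% to 97%). If one-tailed 2.5% was intended, the improvement threshold does not move and there is no loss of power.
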